#### Health literacy

We hypothesize that persons with low health literacy will derive more benefit from navigation than those with higher literacy. The Rapid Estimate of Adult Literacy in Medicine (REALM) for English speakers and the Short Assessment of Health Literacy for Spanish Adults (SAHLSA) will be used to assess health literacy among all subjects at baseline. Less than seventh grade reading level will be considered low-literacy. Secondary analyses will examine health literacy as a continuous variable. This measure is omitted among the few subjects who do not speak English or Spanish.

#### Self-Efficacy

We assess patient self-efficacy among all subjects using the Communication and Attitudinal Self-Efficacy Scale for cancer (CASE)[43]. CASE scores are assessed at baseline, three months, six months, and twelve months for subjects with cancer.

#### Knowledge

We anticipate that navigation will be associated with improvements in knowledge. We will assess knowledge about breast cancer and colorectal cancer and its treatment using instruments developed by our investigators. It will be assessed at baseline for all subjects and at three months for primary care subjects and at six and twelve months for subjects with cancer.

#### Functional health status

We will assess overall quality of life using the Functional Assessment of Cancer Therapy[44] scales (FACT-C and FACT-B). These will be assessed at baseline among all subjects, at three months among primary care subjects and at six and twelve months among subjects with cancer.

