## Methods/Design

### Study Design

The University of Rochester Patient Navigation Research Program (UR-PNRP) is a National Cancer Institute-funded, 5-year, randomized trial of PN for patients with a new diagnosis of breast or colorectal cancer, or with a positive screening test for these diseases[41]. The primary outcomes of the UR-PNRP are timeliness of care, guideline-concordant care, patient satisfaction, and quality of life.

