**Quality of Life**		
Quality of Life	Impact of Events Scale (IES)	0;3;6;9;12
Cancer Related Health Status	Functional Assessment of Cancer Therapy-Breast Cancer (FACT-B)	0;3;6;9;12
Cancer Related Health Status	Functional Assessment of Cancer Therapy-Colorectal Cancer (FACT-C)	0;3;6;9;12
		
**Medical Conditions**	Charlson Commorbidity	chart review
		

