### Data Analysis

Continuous measures will be compared between randomized groups, using two-sample *t*-tests. These measures include times, mean satisfaction and quality of life scores. Effect sizes are expressed in terms of standard deviations of the measure given that we have no a priori estimates of the distribution parameters. With the noted sample sizes for cancer treatment subjects, the expected sample will provide enough power to detect differences in mean measures of as little as 0.4 standard deviations. Cohen suggests that effect sizes of 0.2, 0.5 and 0.8 standard deviations can be considered "small", "moderate" and "large". We expect to be able to detect moderately-small effects with this analysis and should have power to detect clinically meaningful differences between the groups.

At the conclusion of the trial, analysis will include local as well as multi-institutional outcomes comparisons between intervention and control patients, combining data from multiple institutions performing trials of patient navigation funded by the National Cancer Institute, under the multi-institutional granting structure.

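### The instrument behind quality of life, listed as a primary outcome, is not fixed: Table 1's row label points to the IES, the text to FACT-B/FACT-C, and the planned test names neither

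*Protocol article*

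**What the plan says.** Study Design gives the primary outcomes as "timeliness of care, guideline-concordant care, patient satisfaction, and quality of life". The Discussion expects quality of life to improve and places its formal evaluation at the end of the study.

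Table 1 has a block headed Quality of Life with three rows. The first is the "Impact of Events Scale (IES"), and only this row carries the category Quality of Life. The other two are the "Functional Assessment of Cancer Therapy-Breast Cancer (FACT-B") and the "Functional Assessment of Cancer Therapy-Colorectal Cancer (FACT-C"), both with the category Cancer Related Health Status.

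In the section Functional health status the text reads "We will assess overall quality of life using the Functional Assessment of Cancer Therapy[44] scales (FACT-C and FACT-B"). The IES is named nowhere in the article outside Table 1.

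Data Analysis compares continuous measures between the randomised groups by two-sample t-test and adds: "These measures include times, mean satisfaction and quality of life scores". It names no instrument and does not mention cancer type. It gives a detectable difference of 0.4 standard deviations.

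The FACT assessment times also differ. Table 1 has months 0, 3, 6, 9 and 12, while the text, after baseline, has them "at three months among primary care subjects and at six and twelve months among subjects with cancer". That is a separate inconsistency, and nothing below depends on it.

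**The concern.** An outcome listed as primary needs one score, known before the data are analysed. Here the IES can be presented as the quality-of-life measure on the strength of its row label, and FACT on the strength of the text. The planned test is worded so that it fits either. By title alone, a scale for the impact of events and a functional assessment of cancer therapy are not interchangeable, so they could give different answers. The choice between them could then be made after the results are seen.

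A second, smaller issue follows from FACT itself. Breast and colorectal patients complete different forms, and the only stated method is one unstratified comparison of means. If the two forms have different average scores, that difference adds variance to a comparison that ignores cancer type.

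**Working it through.** **1. The places side by side**

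| Place | What it attaches to quality of life |
|---|---|
| Study Design | Primary outcome, no instrument |
| Table 1, block heading | IES, FACT-B and FACT-C together |
| Table 1, row category | IES only; FACT is cancer-related health status |
| Functional health status | FACT-B and FACT-C; IES absent |
| Data Analysis | Quality-of-life scores, no instrument |

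No place says that one instrument takes precedence.

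**2. The plan's own figure.** Inputs are 0.4 SD (Data Analysis) and 200 projected cancer patients with 80% power (Sample Size Determination). Two-sided 5% and 1:1 allocation are assumed, because the article states neither.

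- Patients per arm: 2 × (1.960 + 0.842)² / 0.4² = 98.1, so 99 per arm or 198 in all.
- Detectable difference with 200 patients: 2.802 × √(4/200) = 0.396 SD.
- Power at 0.4 SD with 100 per arm: Φ(0.4/√(2/100) − 1.960) = Φ(0.868) = 80.7%.
- With the 300 patients also mentioned: 2.802 × √(4/300) = 0.323 SD.

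The 0.4 SD therefore reproduces when all 200 patients enter one comparison. If the 200 were split evenly by form (an assumed split), each form would have 100 patients and a detectable difference of 2.802 × √(4/100) = 0.56 SD. The stated figure implies a single comparison across both cancers.

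**3. Two candidate instruments.** Each is tested at an assumed two-sided 5%, and either may carry the claim. With independent tests the chance of at least one false positive is 1 − 0.95² = 9.75%. For correlated test statistics, simulated as bivariate normal with 400,000 draws:

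| Assumed correlation | Chance of at least one false positive |
|---|---|
| 0.3 | 9.5% |
| 0.5 | 9.1% |
| 0.7 | 8.4% |

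**4. Pooling the two forms without adjustment.** Take a within-form SD of 1, a gap of s SD between the form means, and a share p of patients on one form. The pooled SD is √(1 + p(1 − p)s²), and power with 100 per arm is Φ(0.4/(SD × √(2/100)) − 1.960). The article gives neither s nor p, so both are assumed.

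| Gap s | Share p | Pooled SD | Power |
|---|---|---|---|
| 0 | any | 1.000 | 80.7% |
| 0.5 | 0.5 | 1.031 | 78.3% |
| 0.5 | 0.7 | 1.026 | 78.7% |
| 0.5 | 0.8 | 1.020 | 79.2% |
| 1.0 | 0.5 | 1.118 | 71.6% |
| 1.0 | 0.7 | 1.100 | 73.0% |
| 1.0 | 0.8 | 1.077 | 74.7% |

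**The case against.** The strongest reply is that the text already settles the matter. The outcome-by-outcome account defines quality of life once, as FACT, and Data Analysis follows it directly. Table 1 also covers measures that are not outcomes, so a row there does not make the IES one. This is a fair reading and probably the intended one, which is why the fix adopts FACT. It does not remove the row label, however, and the sentence on the t-tests would fit the IES equally well.

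A reader might infer that Table 1 and the text say opposite things. They do not: FACT-B and FACT-C stand under the same Quality of Life block heading as the IES. The inconsistency lies in the row categories and in the text's silence on the IES.

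A reader might also infer that raw FACT-B and FACT-C totals will be averaged, and that a chance imbalance in tumour mix would distort the result. No section says that raw totals are pooled, and scoring detail is commonly left to the full protocol or SAP. Under randomisation such an imbalance is chance variation that the t-test's variance already contains, so the cost is precision and not bias. The inference that the two cancers are compared together rests on the 0.4 SD figure, which is given for continuous measures in general and not for FACT specifically.

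The power loss in the working is for the 200 projected patients. The article reports 344 recruited. If all were cancer patients in equal arms, power at 0.4 SD would be 96.0%. With a 1 SD gap and an even split it would be Φ(0.4/(1.118 × √(4/344)) − 1.960) = 91.3%, a smaller loss.

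Finally, the planned analytic sections leave quality of life off the primary list and make functional health status secondary. That conflict over status is a separate matter and should not add weight to this one. Arguments from the instruments' scoring direction or shared items are not used, because the article gives neither.

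**Conclusion.** The point stands as an inconsistency in the article. Quality of life is called primary in Study Design, two kinds of instrument can claim the name, and the planned test does not choose between them.

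If a positive result on either would be reported as a quality-of-life benefit, the false-positive chance is about 8.4% to 9.75% against a nominal 5%. This assumes two-sided 5% tests and a correlation between 0.7 and 0. Nothing in the article says that either result would be so claimed; it only leaves that open.

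The effect of the two FACT forms is secondary and is one of precision only. At 200 patients, power falls from 80.7% to about 78–79% for an assumed 0.5 SD gap between forms, and to about 72–75% for an assumed 1 SD gap, with 50% to 80% of patients on one form. The 0.4 SD figure itself is correct for 200 patients and does not depend on which instrument is meant.

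**What to change.** Before analysis:

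- Name FACT, as Functional health status already does, as the single quality-of-life instrument, and use that definition in Study Design, Table 1, Functional health status and Data Analysis.
- Relabel the IES row in Table 1 as a separate secondary outcome, and state that it does not count as the quality-of-life result.
- Make the FACT comparison on a score common to both forms if one is available. Otherwise use scores standardised within form, with the arms combined for the standardisation. In either case stratify or adjust by cancer type.
- Report form-specific items by cancer type only.

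The cost is a few changes of wording, one rescoring step on data already scheduled for collection, and slightly more analysis work. The small downside is that form-specific items drop out of the pooled comparison if a common score is used. The article describes the study as ongoing, with quality of life to be evaluated at its end, so the choice can still be made without sight of results.

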### Sample Size Determination

Sample size calculations were calculated for time to completion of treatment for diagnosed cancer patients, specifically to assess differences between the intervention and control groups in the proportion of patients who complete treatment at nine months. We estimate that 75% of control subjects will have completed cancer treatment at 9 months. Based on our original projection of 200 enrolled cancer patients, we have 80% power to detect a difference in treatment completion rates of as little as 16% between the navigated and standard care patients. With 300 enrolled cancer patients, this detectable difference improves to 13%. These detectable effect sizes are clinically meaningful. These estimates also apply to any of the outcomes involving proportions such as rates of patient adherence or receipt of guideline concordant care.

### Data Analysis

Continuous measures will be compared between randomized groups, using two-sample *t*-tests. These measures include times, mean satisfaction and quality of life scores. Effect sizes are expressed in terms of standard deviations of the measure given that we have no a priori estimates of the distribution parameters. With the noted sample sizes for cancer treatment subjects, the expected sample will provide enough power to detect differences in mean measures of as little as 0.4 standard deviations. Cohen suggests that effect sizes of 0.2, 0.5 and 0.8 standard deviations can be considered "small", "moderate" and "large". We expect to be able to detect moderately-small effects with this analysis and should have power to detect clinically meaningful differences between the groups.

At the conclusion of the trial, analysis will include local as well as multi-institutional outcomes comparisons between intervention and control patients, combining data from multiple institutions performing trials of patient navigation funded by the National Cancer Institute, under the multi-institutional granting structure.

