### Data Collection

Patient information is collected by research assistants prior to randomization. Patient demographic information is obtained from medical records and patient self-report, via in-person interview. Outcome measures are collected for both intervention and control patients at baseline and at three month intervals, as detailed in Table 1. In addition, information on barriers to care was collected by patient navigators, in the intervention group only, during semi-structured interviews with patients. A standardized form was used. Navigators also keep detailed records of their activities performed on behalf of their caseload of navigated patients, and the time each activity took.

**Table 1 T1:** Outcome and Other Measures of the Patient Navigation Research Program

Category	Title	Collection Times (mo)

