#### Health care satisfaction

We hypothesize improvements in satisfaction with health care. Baseline satisfaction is measured using a newly created patient satisfaction with cancer care (continuous measure). It is assessed at baseline for all subjects and at three months for primary care subjects and at three months, six, nine and twelve months for subjects with cancer or at the end of treatment.

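### Satisfaction and quality of life are to be compared by t-tests that leave the pre-randomisation scores unused, and the article's visit schedules for FACT and self-efficacy contradict Table 1

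*Protocol article*

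**What the plan says.** **Analysis.** Under Data Analysis: "Continuous measures will be compared between randomized groups", by two-sample t-tests. The section continues: "These measures include times, mean satisfaction and quality of life scores". It claims "enough power to detect differences in mean measures of as little as 0.4 standard deviations" for the cancer patients. No baseline covariate is mentioned.

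**Status of the outcomes.** Satisfaction is primary under Study Design, in Table 1 and under Planned Analytic Approach. Quality of life is primary under Study Design. Functional health status, which is measured by FACT, is in the list of secondary outcomes that precedes the Guideline concordant cancer care subsection.

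**Baseline.** Under Data Collection, "Outcome measures are collected for both intervention and control patients at baseline and at three month intervals". That section and Description of the Navigation Intervention both place baseline collection before random assignment.

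**Schedules for cancer patients.** Table 1 gives satisfaction, FACT-B, FACT-C and the self-efficacy scale (CASE) at months 0, 3, 6, 9 and 12. The Functional health status subsection has FACT at baseline for everyone, then "at three months among primary care subjects and at six and twelve months among subjects with cancer". The Self-Efficacy subsection lists baseline and months 3, 6 and 12. The Health care satisfaction subsection has follow-up "at three months, six, nine and twelve months for subjects with cancer or at the end of treatment".

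**The concern.** There are two linked problems.

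1. A two-sample t-test of follow-up scores sets aside a measurement that every patient gives on the same scale before allocation. Patient-reported scores usually correlate with their own baseline, so part of the variance in the comparison could be removed at no cost in patients. One of the affected outcomes is named primary throughout the article.

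2. A reader cannot tell which scores will exist. For cancer patients it is unclear whether FACT is collected at months 3 and 9, or CASE at month 9. For satisfaction, the end-of-treatment option ties an assessment to an event that is itself a target of the intervention, since time to completion of treatment is a primary outcome. If such scores entered the tested comparison, the arms could be measured at different times since randomisation, and a difference in timing could pass for a difference in satisfaction.

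**Working it through.** **Inputs.** From Sample Size Determination: 200 cancer patients as first projected, or 300, taken as 100 or 150 per arm. Recruitment so far supports equal arms: 178 intervention and 344 − 178 = 166 control. From Data Analysis: an effect of 0.4 SD, so SD = 1. Assumed: two-sided 5%, and 80% power, which the article states only for the comparison of proportions. Also assumed: baseline-outcome correlation r of 0.3, 0.5 or 0.7, because the article gives none.

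**Step 1: the plan's own figure.** Detectable difference = (1.960 + 0.842) × √(2/n).
- n = 100: 2.802 × 0.1414 = 0.396 SD. Power at 0.4 SD is 80.7% (80.4% with the noncentral t), and 99 per arm are needed for 80%.
- n = 150: 2.802 × 0.1155 = 0.323 SD. Power at 0.4 SD is 93.4%.

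The stated 0.4 SD is therefore reproduced, and belongs to the 200-patient projection and one unadjusted comparison.

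**Step 2: with baseline adjustment.** Analysis of covariance leaves residual variance 1 − r², so the detectable difference is multiplied by √(1 − r²).

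| r | √(1 − r²) | 100 per arm | 150 per arm | Power at 0.4 SD, 100 per arm | n per arm for 0.4 SD |
|---|---|---|---|---|---|
| none (t-test) | 1 | 0.396 | 0.323 | 80.7% | 99 |
| 0.3 | 0.954 | 0.378 | 0.309 | 84.3% | 90 |
| 0.5 | 0.866 | 0.343 | 0.280 | 90.4% | 74 |
| 0.7 | 0.714 | 0.283 | 0.231 | 97.7% | 51 |

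**Step 3: if the t-test were meant for change from baseline.** The variance is then 2(1 − r), and the detectable difference at 100 per arm is 0.469, 0.396 or 0.307 SD for r = 0.3, 0.5 or 0.7. Each is larger than the covariance-adjusted value.

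**Step 4: schedules side by side, cancer patients, in months.**

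| Scale | Table 1 | Text | Agreement |
|---|---|---|---|
| Satisfaction | 0, 3, 6, 9, 12 | 0, 3, 6, 9, 12, or end of treatment | Visits agree; end of treatment is added |
| FACT-B, FACT-C | 0, 3, 6, 9, 12 | 0, 6, 12 | Months 3 and 9 conflict |
| CASE | 0, 3, 6, 9, 12 | 0, 3, 6, 12 | Month 9 conflicts |

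Months 6 and 12 appear in both versions for all three scales.

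**The case against.** The strongest reply is that nothing here is invalid. Randomisation makes the t-test unbiased without adjustment, the 0.4 SD is correct, and at 150 per arm the unadjusted test already has 93.4% power for it. This stands. The complaint is one of efficiency, its size depends on a correlation the article does not give, and in power terms it matters less if 300 cancer patients are enrolled. The gain in precision remains, however, and the data for it are already scheduled.

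A second reply is that a condensed article may leave the choice of analysis visit to an analysis plan. That also stands, so the absence of a named visit is not itself the point. The t-test is a stated choice, and the contradictory schedules are errors within this document.

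A reader might go further than the text allows in five places:
- **Separate tests at each follow-up visit, with an inflated error rate.** The article does not plan these. It names neither a visit nor a series of tests.
- **FACT-B and FACT-C pooled in one raw mean.** The article lists them separately and says nothing about pooling.
- **A conflict for the knowledge instruments.** Table 1 gives months 0, 3 and FU, and the text gives month 3 for primary care subjects and months 6 and 12 for cancer subjects. FU is undefined, so the two can agree.
- **Biased satisfaction results.** The end-of-treatment phrase could mean an additional score, a replacement or a stopping point. Bias would arise only if such scores entered the tested comparison.
- **Table 1 as the correct schedule.** Nothing in the article shows which version was followed.

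**Conclusion.** The point holds as a loss of precision plus a set of contradictions to repair. For satisfaction and quality of life, the stated t-tests forgo a reduction in the detectable difference of about 5%, 13% or 29% at r = 0.3, 0.5 or 0.7 (1 − 0.954, 1 − 0.866, 1 − 0.714). This is from about 0.40 to 0.38, 0.34 or 0.28 SD at 100 per arm, and from about 0.32 to 0.31, 0.28 or 0.23 SD at 150 per arm. These figures assume two-sided 5%, 80% power, equal arms, complete data and a linear relation to baseline. Separately, the FACT schedule and month 9 of CASE contradict Table 1 for cancer patients, and the satisfaction wording admits a score timed by an event the intervention aims to move. The documents do not support a claim that the analysis is invalid or that its power figure is wrong.

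**What to change.** - Replace the two-sample t-tests for these scales by a baseline-adjusted comparison: analysis of covariance, or a repeated-measures model with the baseline score as covariate.
- Name one contrast per scale, at visits timed from randomisation. Months 6 and 12 are in both versions of the schedule, so a contrast at either does not depend on how the conflict is settled.
- State what the end-of-treatment satisfaction score is, and keep it out of that contrast.
- Reconcile Table 1 with the Self-Efficacy and Functional health status subsections according to what was actually collected, rather than presuming that either is right.

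The cost is a little analysis work and some wording, with no new data. The article describes the study as ongoing and puts the formal evaluation of satisfaction and quality of life at its end, so the change can still be made before the comparison is run.

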### Planned Analytic Approach

The primary outcome measures for this clinical trial include time to completion of treatment (or to diagnostic resolution in the case of patients with positive screening tests), patient satisfaction, and cost. Details regarding each of these measures are as follows:

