#### Time to completion of cancer treatment

This measure is defined based on review of medical records following completion of treatment for oncology subjects. It will be assessed based on time (in days) from the date of the initial oncology/surgical consultation to completion of cancer treatment (e.g. surgery, chemotherapy regimen, or radiation, whichever occurs last).

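### Time to completion of treatment, a primary outcome, is to be compared by a two-sample t-test, although patients who have not completed treatment have no time to enter.

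*Protocol article*

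**What the plan says.** All references are to the protocol article.

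- **Status.** Planned Analytic Approach: "The primary outcome measures for this clinical trial include time to completion of treatment".
- **Definition.** Time to completion of cancer treatment: the outcome is "time (in days) from the date of the initial oncology/surgical consultation to completion of cancer treatment", ending with whichever treatment comes last. On ascertainment: "This measure is defined based on review of medical records following completion of treatment for oncology subjects". No value is given for a patient who does not complete, and no date at which chart review closes.
- **Sizing.** Sample Size Determination: "Sample size calculations were calculated for time to completion of treatment for diagnosed cancer patients", through "differences between the intervention and control groups in the proportion of patients who complete treatment at nine months". The control assumption is: "We estimate that 75% of control subjects will have completed cancer treatment at 9 months". The detectable differences are 16 points with 200 cancer patients and 13 points with 300, at 80% power.
- **Analysis.** Data Analysis: continuous measures go to two-sample t-tests, and "These measures include times, mean satisfaction and quality of life scores". A detectable difference of 0.4 standard deviations is attached to these tests. Neither censoring nor a time-to-event method is mentioned.

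**The concern.** A t-test needs an observed number for every patient it compares. Under the article's definition, a patient who has not completed treatment has none. Unless some value is assigned, and none is described, the comparison runs among completers.

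That would matter little if few patients were unfinished and the share were the same in both arms. The sizing assumes the opposite: 25% unfinished among controls at 9 months, and 9% (16-point target) or 12% (13-point target) among navigated patients. Navigation is meant to improve adherence and follow-through, so whether a patient has a time at all is itself affected by the intervention. Randomisation does not protect a comparison of two groups selected in that way.

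Two kinds of harm are possible. If navigation speeds everyone up, an early cut-off hides the slow finishers, mostly in the control arm, and the difference shrinks. If navigation instead brings people to completion who would otherwise not have finished, and they finish late, the mean among navigated completers rises and a benefit can look like a delay.

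This is a method that the article writes down for a primary outcome. It is not a detail left to a fuller document.

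**Working it through.** **1. The plan's own figures.** Two-sided 5% and 1:1 allocation are assumed, as neither is stated. Per arm, n = [1.96·√(2p̄q̄) + 0.842·√(p₁q₁ + p₂q₂)]² / d², then the continuity correction.

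- 75% vs 91%: 86 per arm, 98 corrected, so 196 in total (stated: 200).
- 75% vs 88%: 139 per arm, 154 corrected, so 308 in total (stated: 300).
- 0.4 SD: 2·(2.802/0.4)² gives 99 per arm, so 198 in total (in line with 200).

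The sizing is sound. The 0.4 SD figure needs all 200 patients to contribute a time. With 75 and 91 contributors out of 100 per arm it becomes 2.802·√(1/75 + 1/91) = 0.44 SD. The smaller count is thus a minor cost; the main problem is which patients are left.

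**2. Uniform speed-up.** Inputs from the article: 75% vs 88% complete at 9 months (taken as 274 days), 150 per arm. Assumed: the time distribution (exponential, or Weibull with shape 2 or 3) and the chart cut-off. Power of the completers-only t-test by simulation:

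| Chart cut-off | Completers-only t-test | Log-rank, non-completers censored |
|---|---|---|
| 9 months | about 30–34% | about 92–96% over all cut-offs |
| 12 months | about 54–82% | |
| 18 months | about 79–93% | |

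Repeat runs move these figures by one or two points. At 12 and 18 months the low end is the exponential. At 9 months the three distributions hardly differ.

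Check on the log-rank figure at 9 months: hazard ratio ln(0.12)/ln(0.25) = 1.53; completions 150·0.75 + 150·0.88 = 244.5. Schoenfeld power is Φ(√(244/4)·ln 1.53 − 1.96), about 91%, in line with the simulation.

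The shrinkage is visible too. With exponential times and a 12-month cut, completers show about 23 days of a true 68-day difference in means. Under shape 2 with an 18-month cut they show about 38 of 39 days.

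**3. Navigation adds late finishers only.** Assumed: 75% of each arm finishes with a mean of 160 days, and navigation adds 13 points who finish around day 240.

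- Control completers' mean: 160 days.
- Navigated completers' mean: (75·160 + 13·240)/88 = 15,120/88 = 171.8 days.

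Navigation has raised completion from 75% to 88%, yet completers look about 12 days slower. With 150 per arm and an SD of 20 days among the late finishers, the t-test finds navigation significantly slower in about 54% of simulated trials if the SD of the other times is 40 days, and in about 21% if it is 80 days. It almost never finds navigation faster.

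A similar scenario at 75% vs 91% and 100 per arm (late finishes spread over days 210–274, the others around day 170 with SD 50) gives a lengthening of 12.6 days, significant against navigation in 35% of trials. There the log-rank test has only about 44% power, while the 9-month proportion test has 87%. Both point the right way. That is why the proportion should be reported beside the time-to-event analysis.

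**The case against.** The strongest reply is that the article nowhere says non-completers are excluded. Reading charts after completion may only describe when they are read. With no cut-off given, charts could be followed until nearly everyone has finished. This stands in part. The 25% is the control share unfinished at 9 months, and a reader who infers that a quarter of controls never contribute a time goes beyond the text. With an 18-month cut and a shape 2 or 3 distribution, almost all of the power returns. Patients who die, stop or are lost would still have no time.

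Four further inferences are tempting and not supported:

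- **That reversal is to be expected.** It needs an effect mainly on whether patients finish. The article also describes navigators acting early to prevent delays, which suggests a speed-up, and then the direction is kept.
- **That the stated power belongs to a comparison nobody planned.** The sizing section names the 9-month proportion as what it assesses, and the t-tests have their own detectable effect. No test is named for any proportion, which may only reflect a condensed article.
- **That treatment times and diagnostic times are pooled.** The article says "or to diagnostic resolution in the case of patients with positive screening tests), patient satisfaction, and cost". This gives an alternative endpoint for a different population; pooling is not stated.
- **That the analysis must be stratified by tumour type.** This is a reasonable preference, but its absence is no error.

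**Conclusion.** The point holds. The written test for a primary outcome cannot use every randomised cancer patient under the article's own definition, and its own sizing assumes that unfinished treatment differs between arms.

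The consequence ranges from slight to serious. Under a uniform speed-up it is lost power and a shrunken estimate: severe with a 9-month cut, small if charts run to 18 months and times are not close to exponential. Under an effect that mainly adds late completers, the sign can reverse. All power figures rest on assumed distributions, cut-offs, 1:1 allocation and two-sided 5%, and on non-completers entering without a value. That last step is an inference from the definition and from what a t-test requires.

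Because the outcome is primary and the rule is written, it should be corrected before the data are analysed.

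**What to change.** 1. Take time to completion of cancer treatment out of the list of measures compared by t-test.
2. Analyse it in all randomised cancer patients by Kaplan-Meier with a log-rank test or Cox model, censoring non-completers at last follow-up. Treat death before completion as a competing event, so that the reported completion curves are cumulative incidences where deaths occur.
3. State the chart-review cut-off, and how patients who stop treatment for good enter the analysis.
4. Report the difference in proportion complete at 9 months, the quantity that was sized, among all randomised cancer patients with its confidence interval. Say how patients lost before 9 months are counted.

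The cost is a change of wording, plus last-contact or death dates for non-completers taken from charts already under review. No change to recruitment, visits or sample size is needed.
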